## Abstract

**Introduction:**

Primary ciliary dyskinesia (PCD) is a rare, genetic, multiorgan disease with an estimated prevalence of 1 in 10 000. It affects mainly the upper and lower airways due to impaired mucociliary clearance. Almost all patients have sinonasal or otologic (ear–nose–throat, ENT) problems, although the ENT clinical phenotype may present great variability. Despite that, data on PCD ENT manifestations are scarce and based on small single-centre studies. To date, we know little about the spectrum and severity of PCD ENT disease, its association with lung disease, its course over life and its determinants of prognosis.

This study protocol describes the aims and methods of the first prospective, observational, multinational cohort study focusing on ENT disease in patients with PCD.

**Methods and analysis:**

The ENT prospective international cohort of patients with PCD (EPIC-PCD) is a prospective standardised observational clinical cohort set up as a multinational multicentre study, embedded into routine patient care. It aims to longitudinally characterise ENT disease in patients with PCD and its association with lung disease, and to identify determinants of its prognosis. Patients of all ages, diagnosed with PCD who undergo an ENT clinical assessment at least once a year at one of the participating centres will be invited to participate. Collected data include diagnostic test results, results of ENT examinations, lung function measurements, information on management of ENT disease and patient-reported data on clinical symptoms and health-related quality of life (QoL). Data are collected using the standardised PCD-specific FOLLOW-PCD form and the validated QoL-PCD questionnaire.

**Ethics and dissemination:**

The study has been reviewed and approved by the Human Research Ethics Committees at all participating centres, based on local legislation. The results of the study will be published in scientific journals, presented at scientific conferences and disseminated to participants and national patient organisations.

**Trial registration:**

NCT04611516.

Strengths and limitations of this studyThe ear–nose–throat prospective international cohort of patients with primary ciliary dyskinesia (EPIC-PCD) is the first prospective international multicentre clinical study focusing on upper airways disease in patients with PCD.The study is embedded in routine patient care, which allows recruitment of large numbers of patients, necessary in rare diseases research.The study combines objective assessments of the upper airways and patient-reported information on symptoms and health-related quality of life (QoL), all collected with disease-specific tools, in a standardised way.The cohort aims to be representative of paediatric and adult patients with PCD, followed up at established PCD clinical centres; however, it will not represent patients with atypical symptoms who remain undiagnosed or live in areas where diagnosis and care of PCD is not well established.The EPIC-PCD has the potential to become a valuable research resource in order to help understand better the disease and to improve diagnosis, clinical care and QoL of patients with PCD.

## Introduction

Primary ciliary dyskinesia (PCD) is a rare genetic, multiorgan disorder affecting approximately 1:10 000 individuals.^1 2^ Mutations in disease-causing genes result in defects in ciliary structure or function, leading to a wide range of symptoms from different organ systems.^3–5^ The clinical phenotype of the disease is heterogeneous; however, reduced airway mucociliary clearance predisposes almost all affected individuals to recurrent upper and lower respiratory infections.^6 7^

Persistent symptoms from the upper airways and ears (ear–nose–throat: ENT) are a common characteristic of most patients with PCD. Ear symptoms commonly present in children with PCD as severe and bilateral otitis media with effusion (OME).^8–11^ OME usually resolves spontaneously in otherwise healthy children, but in PCD it seems to persist longer and might need specific management.^8 12–15^ In some cases, persistent OME may lead to hearing impairment and cause delays in speech development.^16 17^ A newly published study evaluated 47 children in two PCD centres in North America and found that 52% of children with PCD-related hearing loss were not aware of their hearing deficit that was present on audiological assessment.^18^ While otologic involvement seems to improve with age in patients with PCD, sinonasal disease appears to persist and may worsen in adulthood.^19^ First manifestations appear sometimes soon after birth and are usually non-specific in the form of rhinitis and episodic facial pain due to recurrent infections leading gradually to chronic rhinosinusitis (CRS).^20–24^ In adults, a recent study identified sinonasal disease as a primary cause of decreased quality of life (QoL) in patients with PCD.^19^ Hypoplasia and agenesis of paranasal sinuses have also been described, while nasal polyps are more common in patients with PCD compared with the general population, although this complication has not been well characterised.^19 25 26^

Despite being so frequent and impairing patients’ physical health and QoL, data on ENT disease in PCD are still scarce. Several large national and multinational research collaborations have made important advances in PCD research in the recent years, though most clinical studies focus on improving diagnosis and characterising lung disease.^27–30^ Only few retrospective and single-centre studies have described ENT manifestations in some details. Most studies focused on children and little is known about age-related changes,^8 13^ while studies, including standardised sinonasal and otologic evaluations, were rare. We lack knowledge about the spectrum and severity of ENT disease in patients with PCD, its association with lung disease, its course over life and determinants of prognosis.

This study protocol describes the aims and methods of the first prospective, observational, multinational cohort study focusing on ENT disease in patients with PCD.

### Study objectives

This study aims to characterise ENT disease in patients with PCD and its association with lung disease, and to identify determinants of its course and prognosis. Specifically, we aim to: (a) assess the prevalence and severity of sinonasal and otologic symptoms and the frequency and range of signs and physiological findings assessed during standardised ENT physical examination, and describe possible differences by age; (b) study the association of sinonasal and otologic disease with lung disease in patients with PCD and (c) identify determinants of the course and prognosis of sinonasal and otologic disease in patients with PCD.

## Methods and analysis

### Study design

The ENT prospective international cohort of patients with PCD (EPIC-PCD) is a prospective observational clinical cohort set up as a multinational multicentre study. It is embedded into routine patient care of participating reference centres for PCD and patients continue to be managed according to local procedures and protocols. The study is hosted at the Institute of Social and Preventive Medicine (EPIC-PCD data centre) at the University of Bern, Switzerland, and is managed in collaboration with participating centres (EPIC-PCD clinics).

Patient data are collected prospectively. Baseline information is collected at the enrolment of the patient in the study and follow-up data during clinical follow-up visits at the participating centres. The study has no foreseen endpoint. Patient follow-up is planned for a minimum period of 4 years; however, it will be extended if collaborators agree.

### Study population

#### Inclusion criteria and participating centres

Patients of all ages, diagnosed with PCD, according to the European Respiratory Society (ERS) guidelines, and followed-up at one of the participating centres, are invited to participate in the EPIC-PCD.^27^ Patients are excluded if they do not undergo an ENT clinical assessment at baseline and at least once a year during the study period.

Patient recruitment has started at the following centres (EPIC-PCD clinics; figure 1):

University Hospital Bicêtre Paris-Sud, France.Centre Hospitalier Intercommunal Creteil and University Hospital Henri Mondor, France.Hospital Universitario La Fe in Valencia, Spain.University Hospital of Southampton, UK.University Hospital of Leuven, Belgium.VU University Medical Center in Amsterdam, the Netherlands.University of Cyprus;Hacettepe University in Ankara, Turkey;Marmara University in Istanbul, Turkey;University Children’s Hospital Charité-Universitätsmedizin in Berlin, Germany.University Children’s Hospital in Bern, Switzerland.

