#### Clinical assessments

Eligible patients are followed regularly at the EPIC-PCD clinics, at 3–6-month intervals, as planned for clinical reasons, regardless of their participation in the study. Each patient undergoes a detailed sinonasal and otologic examination by ENT specialists, at minimum once a year, during a scheduled follow-up visit. Additional ENT examinations are performed on clinical indication in-between follow-up visits. Patients will not be subjected to additional invasive measurements solely for the purposes of the study; examinations and tests are only done if clinically indicated or as part of the local follow-up protocol. All examinations and tests are performed following the local standard operating procedures of the clinic. The extended study team discusses differences and ensures that collected data are standardised and comparable.

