### What information is collected

Figure 2 provides a brief overview of the information collected from participating patients at the baseline and follow-up visits, including the minimum required data, which are assessed for all patients in all participating centres and additional data from tests performed in few centres and which will be collected if available for subgroup analysis to address additional research questions. Small exemptions are allowed when a minimally required examination was not performed due to, for example, the patient’s very young age, as long as each patient undergoes a specialised ENT examination at least once a year.

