For all analyses, results will be interpreted with caution considering the clinical importance and not just mere statistically significant findings. If needed, we will correct for multiple testing. All missing values will be described in detail; however, we expect this will not be an issue for the important variables as the data are collected prospectively. In case we have significant amount of missing data, we will consider subgroup analyses or multiple imputation of missing data to deal with this issue, depending on what is the most appropriate approach for the specific question and analysis.

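### The exclusion rule rests on yearly ENT attendance over a future, open-ended study period: it cannot be judged at enrolment and, applied literally, would leave only complete attenders

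*Protocol article*

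**What the plan says.** The exclusion sentence, under Inclusion criteria and participating centres, reads: "Patients are excluded if they do not undergo an ENT clinical assessment at baseline and at least once a year during the study period". The abstract (Methods and analysis) words the condition differently: diagnosed patients "who undergo an ENT clinical assessment at least once a year at one of the participating centres will be invited to participate".

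The length of the period comes from Study design: "Patient follow-up is planned for a minimum period of 4 years; however, it will be extended if collaborators agree", and "The study has no foreseen endpoint". Under What information is collected, single examinations may be skipped, for example in a very young child, but only "as long as each patient undergoes a specialised ENT examination at least once a year".

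Clinical assessments describes the yearly examination as normal practice: "Each patient undergoes a detailed sinonasal and otologic examination by ENT specialists, at minimum once a year, during a scheduled follow-up visit". On missing data, Planned analysis and outcomes of interest says "we expect this will not be an issue for the important variables as the data are collected prospectively". It names subgroup analyses or multiple imputation as options if the amount proves significant.

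**The concern.** An eligibility rule should be decidable when the patient is enrolled. Here patients are identified, invited and recruited at a clinic visit, yet one of the two conditions concerns attendance in the years that follow. With no fixed end to the study, that condition is never finally settled for anyone.

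A centre that follows the sentence literally would treat a patient with valid baseline data who later misses a year as excluded. The cohort would then be selected on its own follow-up. The analysis most exposed is the last one planned, which sorts patients into four groups by status at baseline and at 2 years and looks for determinants of group membership. If patients whose ENT problems have settled are less likely to attend, the group that is positive at baseline and negative at 2 years is under-represented. The course of disease then looks more persistent than it is. Missed annual assessments would also drop out of sight, because the patients who missed them would no longer count.

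**Working it through.** The article derives no figure from this rule and states no attendance or dropout rate. There is nothing to reproduce, so the check is mainly of the text, followed by an illustration.

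**Text.**
1. Exclusion sentence: two conditions, baseline and yearly during the study period. The second is forward-looking.
2. Study design: the period is at least 4 years, can be extended and has no foreseen end. The second condition therefore cannot be known at enrolment.
3. Abstract: yearly ENT assessment is a condition for being invited, with no time frame. It can be read as usual care at the centre.
4. What information is collected: the allowance for missed tests keeps the yearly ENT examination as a fixed condition.
5. No section limits the rule to enrolment, says that data gathered before a missed year are kept, or deals separately with dropout or death.

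**Loss of patients (assumed attendance).** If a proportion a attends in any year, independently between years, the share still meeting the rule after y years is a^y.

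| Assumed a | 2 years | 4 years | Of 500 at 2 years | Of 500 at 4 years |
|---|---|---|---|---|
| 95% | 0.95² = 0.9025 | 0.95⁴ = 0.8145 | 451 | 407 |
| 90% | 0.90² = 0.81 | 0.90⁴ = 0.6561 | 405 | 328 |
| 85% | 0.85² = 0.7225 | 0.85⁴ = 0.5220 | 361 | 261 |
| 80% | 0.80² = 0.64 | 0.80⁴ = 0.4096 | 320 | 205 |

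The 500 is the midpoint of the expected 450–550 recruits. The 2-year columns are the relevant ones for the planned course and prognosis analysis.

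**Bias (assumed attendance by ENT status).** With true prevalence p, and yearly attendance a1 in patients with persisting ENT disease and a0 in those without, prevalence among those kept is p·a1^y / (p·a1^y + (1−p)·a0^y).
- p = 50%, a1 = 95%, a0 = 85%: at 2 years 0.9025/(0.9025 + 0.7225) = 55.5%; at 4 years 0.8145/(0.8145 + 0.5220) = 60.9%.
- Same p and a1, with a0 from 90% down to 80%: 52.7% to 58.5% at 2 years and 55.4% to 66.5% at 4 years.
- a1 = a0 = 95%: 50% at both times, so no bias.

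Put as resolution: if 30% truly resolve by 2 years, and 70% of those resolved and 90% of those persistent are kept, observed resolution is 0.30 × 0.70 / (0.30 × 0.70 + 0.70 × 0.90) = 0.21/0.84 = 25%.

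**The case against.** The strongest reply is that this is an entry criterion, loosely worded. The abstract makes yearly ENT assessment a condition for invitation, and the recruitment section speaks of eligible patients being identified and then invited, so eligibility is settled beforehand. On the literal reading an open-ended study could never fix its cohort, yet the baseline description is planned first. This may well be what the authors meant, but the exclusion sentence does not say so. Eleven listed centres, with more to be invited, could apply it differently.

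A reader might go further and infer that dropouts, deaths and recovered patients are removed and their data discarded. The article says none of this; it follows only from literal application. Nor does it support these further inferences:
- *Baseline prevalence is biased.* That would require deleting patients retrospectively from the baseline analysis, which is not stated.
- *Missing follow-up is ignored.* Missing values are to be described in detail, multiple imputation is named, and the planned mixed models can use incomplete series.
- *The cohort of 450–550 is contradicted.* That figure is a feasibility-based recruitment expectation with no power calculation behind it, and later attrition does not conflict with it.
- *The aim of representativeness is contradicted.* The strengths and limitations list says the "cohort aims to be representative of paediatric and adult patients with PCD, followed up at established PCD clinical centres" and discloses who is not represented. A usual-care criterion fits that aim; only literal exclusion for missed years would undercut it.

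Two limits on the bias argument also stand. Yearly ENT examination is scheduled for every patient, so attendance need not follow symptoms. Extra examinations on clinical indication do give symptomatic patients more chances to meet the rule, but a link between attendance and disease remains an inference. And selective missed visits would distort a complete-case 2-year analysis even without this rule, so the illustrated shift is not due to the sentence alone. What literal exclusion would add is the loss of the partial data that mixed models and imputation could use.

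**Conclusion.** The concern holds as a badly fixed eligibility rule. One of its two conditions cannot be known at enrolment, it differs in framing from the abstract, and taken literally it restricts the cohort to complete attenders. The consequence is certain loss of some patients under that reading, and possible bias, chiefly in the 2-year course and prognosis analysis.

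The size cannot be derived from the documents. Every attendance, prevalence and resolution rate used above is an assumption, as is independence between years. The bias vanishes if attendance is unrelated to ENT status. The documents do not show that any patient will in fact be removed, so this is a rule to correct before centres apply it and not evidence that results are already distorted.

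**What to change.** Reword the exclusion sentence so that eligibility uses only what is known at enrolment: confirmed PCD, a baseline ENT assessment, and follow-up at a centre that schedules ENT review at least yearly. Bring the abstract and the sentence on permitted exemptions into line with it.

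Add one statement that enrolled patients and their data are kept whatever visits they later miss. Treat missed years and dropout as missing follow-up within the mixed models and multiple imputation already named, and end follow-up at death. Further detail on handling missed visits can stay in the full protocol or analysis plan.

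The cost is a sentence or two of text, with no extra visits or tests. The downside is that reported follow-up completeness will look less favourable, because missed years will be visible.

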**Figure 1 F1:**
[figure not shown]
Centres currently participating to the EPIC-PCD cohort study. The EPIC-PCD clinics are marked with a black dot and the EPIC-PCD data centre with a yellow dot. EPIC-PCD, ear–nose–throat prospective international cohort of patients with primary ciliary dyskinesia.

After the establishment of the study in these initial EPIC-PCD clinics, we will invite more PCD centres to join the study and begin patient recruitment.

### Study procedures

#### Patient identification and recruitment

Eligible patients are identified and invited to participate in the study, and receive all study information by the local clinical team at the EPIC-PCD clinics. Patients are recruited during a clinical follow-up visit; there might be small variations in recruitment and data collection between participating centres to allow the study to be embedded in the regular clinical routine.

#### Clinical assessments

Eligible patients are followed regularly at the EPIC-PCD clinics, at 3–6-month intervals, as planned for clinical reasons, regardless of their participation in the study. Each patient undergoes a detailed sinonasal and otologic examination by ENT specialists, at minimum once a year, during a scheduled follow-up visit. Additional ENT examinations are performed on clinical indication in-between follow-up visits. Patients will not be subjected to additional invasive measurements solely for the purposes of the study; examinations and tests are only done if clinically indicated or as part of the local follow-up protocol. All examinations and tests are performed following the local standard operating procedures of the clinic. The extended study team discusses differences and ensures that collected data are standardised and comparable.

### Data collection instruments

For the collection of patient data, we use standardised PCD-specific instruments, specifically FOLLOW-PCD and QoL-PCD.

#### FOLLOW-PCD

It is a disease-specific form for standardised prospective data collection during routine clinical follow-up of patients with PCD.^31^ It was developed by a multidisciplinary, international working group of the better experimental approaches to treat PCD (BEAT-PCD) COST action network.^28 32^ FOLLOW-PCD has a modular structure, which permits different members of the clinical team (pulmonologists, ENT physicians, diagnostic experts, physiotherapists, lung function technicians, etc) to complete different modules. FOLLOW-PCD consists of seven modules that enable an extensive evaluation at baseline and annual reviews, when all modules are completed, and a shorter evaluation at routine (eg, 3 monthly) follow-up, where only a few modules are used. For the EPIC-PCD study, we use specific modules to collect clinical data relevant to the study, particularly demographic and diagnostic information, results of the physical ENT examination, results of clinical tests and data on hospitalisations and treatments related to the upper airways.

Some modules of FOLLOW-PCD have been developed into patient questionnaires (FOLLOW-PCD questionnaire) that can be completed by the patients during each clinical follow-up visit. The FOLLOW-PCD questionnaire includes detailed questions on frequency and severity of upper and lower respiratory symptoms and health-related behaviours (eg, smoking and exercise).^31^ There are three age-specific versions of the questionnaires: one for adult patients, one for adolescents 14–18 years old and one for the parents or caretakers of patients aged less than 14 years. The FOLLOW-PCD questionnaire has been originally developed in English, German and Greek and is translated in additional languages using a standardised procedure.

In addition to the FOLLOW-PCD questionnaire, we will ask the patients to complete once a year the QoL-PCD, a disease-specific, health-related QoL instrument for PCD, validated and translated in several languages.^33–36^ There are four different versions available for (a) children (6–12 years), (b) adolescents (13–17 years), (c) adults (≥18 years) and (d) a parent-proxy measure for children ≤12 years. The different versions of the questionnaire are divided into 7–10 hypothesised scales generated by multitrait analysis. All versions include two scales about upper respiratory symptoms, and ears and hearing symptoms, which are particularly relevant to this project. The QoL-PCD has demonstrated good internal consistency and test–retest reliability, and is a valuable tool for observational and interventional studies in PCD.

The FOLLOW-PCD questionnaire does not address QoL; therefore, the two questionnaires provide important complimentary information. Both questionnaires have been translated in the local language of each participating EPIC-PCD clinics.

Lastly, some centres use as part of their regular patient follow-up the Sino-Nasal Outcome Test-22 (SNOT-22) questionnaire that assess sinusitis-related QoL.^37^ In these centres, we will also record the SNOT-22 score at baseline and at follow-up for all participating patients.

